#### Possible risks and burdens

This is a long term intervention that requires children and parental attendance tothe scheduled sessions as well as to the assessment appointments for the evaluation of the short, medium and long term effects. The risk of abandonment is high but we will try to reduce it by providing constant feedback to participants and their families.

On the other hand, our previous experience shows that the potential physical risks in the study are minimal. Further, the physical sessions for children have been designed and chosen especially for them. Attention has been put on enjoyment and on lack of excessively (physical and psychological) challenging situations, as well as on trying to minimize the risk of injury, even if this cannot be eliminated completely. Moreover, sessions have been scheduled to avoid overloading children. In the case that of one of these situations happens, the child will immediately be derived to their paediatrician or specialist.

## Discussion

To the authors’ knowledge, this is the first intensive family-based behavioural multi-component intervention for childhood obesity management led from the healthcare paediatrician with a longitudinal design in Spain. It targets the same principal contents for both parents and children in the easiest manner for each age group, focusing on their posterior application in their home unit. The study aims to establish a long-term healthy behaviour related to achieving a healthy weight status, physical activity and eating behaviour in order to improve their quality of life and reduce possible health problems. The study design is a randomized controlled multicenter clinical trial using two types of treatment (Nereu and Counseling) with follow-up measurements at 9, 15 and 21 months after the intervention. We believe that our study is in agreement with the principal recommendations, mentioned by Oude Luttikhuis [17], where it is recommended for family interventions to combine diet, physical activity and behavioural components focused on behavioural changes with good methodological interaction and assessing the effects in a long term period [7]. In addition, the present study has a longitudinal design with a long-term follow-up, and as it is well known, it makes it possible to gather a higher level of evidence than a cross-sectional analysis.

Following the previous editions of the Nereu program, we expect a low drop-out and the probable drop-out rate/percentage has been contemplated in the sample size. However, if we have a high drop-out and we do not achieve the sample provided, it could occur that, the outcome variables do not become statistically significant due to the lack of statistical power. However, we must take into account that paediatricians use the Healthy Child Programme which computerizes medical records of all children, and also during the recruitment period paediatricians can look for a higher sample of children if required. In the recruitment period contamination between groups could occur, as children are randomized from the same healthcare centre or district. We are going to try to prevent this by doing the NP in an external school facility and the assessment periods will be undertaken on different days.

The results from the present study will provide new scientific evidence of the long-term effects of the childhood obesity management, as well as help to know the impact of the present intervention as a health intervention tool for healthcare centres.

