		11	Overcome specific barriers	Giving options to eat on specific days (Christmas, restaurants…)	Ticket-aaaa!!! Eating out side!!
		12	Social support and change	Behaviour modification strategies day-to-day	Where are we going next weekend?
		13	Provide instructions about healthier food	knowledge about how to interpret advertising and how buy food	Let’s go to buy!
		14	Provide feedback on performance	Ways in which they can incorporate PA into their lifestyle.	Why do we use the elevator?
		15	Encouragement and setting goals on PA and nutrition	Setting medium-term goals (behaviour strategy session II)	
			Maintaining behaviour strategies		
**3rd Term (April-Mai) Committing and keeping up**	Autonomy (**Reproduction**)	16	Provide knowledge about healthier eating	Learning to make a balanced menu	How do a balanced menu?
		17	Specific encouragement	Relation between PA and food intake	Burning sweets!
			Decisional balance		
	Evaluation (**Motivation**)	18	Self PA evaluation	Evaluating the implementation of PA	How active are we?
		19	Self-Diet evaluation	Evaluating the implementation of Diet	How well you eat?
		20	Encouraging PA and nutrition	Keeping up medium and long-term behaviour (behaviour strategy session III)	
			Maintenance behaviour strategies		
	Closure	21	Enjoying a healthy day together	Closing Party	
**1 each term**	3 weekend extra activities	--	Encouraging active behaviour in an experiential manner and social support	3 extra family physical activities: Ski, FC Barcelona, Aqua party	

The whole intervention will take place in 3 different school centres and health care centres, which have been recruited especially for the intervention and with a strategic localization around the city, in order to facilitate their accessibility. The children’s physical activity sessions will take place using the sport equipments of the school, the theoretical sessions for parents at the same school or at the health care centre next to the school, and the behaviour strategy sessions will be performed in both places. Parents’ and children’s sessions will be performed simultaneously in order to facilitate their attendance. All intervention groups will have a maximum of 15 children and parents.

The 4 structured components are:

a). Physical activity sessions for children

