The physical exercise programme offered to children will consist of 90 sessions (3 sessions per week, each lasting 60 minutes). The main aim of the sessions is to enhance a physical active behaviour, to look for greater enjoyment during physical activity tasks and meet and practise new sports and games in order to keep practising them for a long time.

All sessions are planned to be performed in a friendly uncompetitive atmosphere and adapted to the participants’ needs, because motivating and encouraging obese children to be physically active cannot be achieved following the same approach as for normal weight children [28]. Obese children are physiologically different from those who are normal weight, and they also have significant emotional differences [29]. In that sense, the sessions have been planned by specialists with at least 4 years of experience in physical activity with overweight and obese children and following the physical activity guidelines for children [30-32]. All the sessions will be performed by two coaches who have the sport science degree with specific knowledge and experience in sport treatment for children with overweight and obesity and who have also attended the specific Nereu course. The Nereu course has been addressed specially to teach and help coaches, nurses and physical activity professionals before starting with the intervention, with specific contents about obesity management.

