The family programme consists of 21 theoretical and practical counselling sessions with a duration of 60 minutes each. The sessions will be in group and will take place once a week atthe same time as their children’s sessions, giving the family the opportunity to exchange experiences and establish shared compromises later at home.

The sessions will be carried out by trained nurses and physical activity education professionals skilled inmultidisciplinary behaviour including physical activity, nutrition and healthy behaviours (Table 1).

The overall focus of the parental sessions is to help families to make better healthy behaviour choices mainly in terms of physical activity and nutrition inside the family unit.

c). Behaviour strategy sessions, involving children and parents

The three behaviour strategies sessions for parents and children, one each term, have been planned to reinforce the acquisition of healthier physical activity and eating habits within the family in a more experimental and practical manner (Table 1).

The contents of the family theoretical and practical sessions, the behaviour strategies sessions as well as the assembly of physical activity sessions, are planned mainly according to the Social Cognitive Theory (SCT) of Bandura [35], and the guidelines of several institutions [32,36-38].

d). Weekend extra activities

Additionally, three extra weekend family physical activities (e.g. ski or water party) will be organized, one each term following the school calendar, in order to encourage and achieve this more active behaviour in an experiential way (Table 1). Participants’ friends or relatives will be also invited to take part in the activities, looking for their social and familial support. At the same time, plans are in place to help them to achieve the minimum recommendations of 60 minutes a day of moderate-vigorous physical activity [39].

**Table 2 T2:** Contents of physical activity training for children, family theoretical and practical sessions and behaviour change strategies

**Term**	**Children physical activity sessions**
**1st TERM (October-December) GETTING INFORMED**	Personal knowledge games
	Interaction group activities
	Collaboration games
	Traditional games
	Balance
**2nd TERM (January-March) BECOMING AWARE**	Different kinds of adapted sports without competition
	Games with alternative equipment
	Aerobic games
	Joint mobility
	Strength games

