#### Counselling group

Each family will be offered 8 individual monthly 10-minute-duration meetings. These sessions will take place at the paediatrician’s office and will be delivered by the child’s nurse or/and paediatrician.

The sessions’ contents will be about tips for the promotion of healthy eating and physical activity habits.

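### The contamination safeguard (NP held in an external school) conflicts with the venues given for two NP components and does not cover guests at the weekend activities

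*Protocol article*

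**What the plan says.** The Discussion names the risk: "contamination between groups could occur, as children are randomized from the same healthcare centre or district". It then gives two measures. The first concerns venue: "We are going to try to prevent this by doing the NP in an external school facility". The second concerns timing: the groups' assessment dates are to be kept apart.

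The Nereu programme section, after Table 1, describes the venues differently. It begins: "The whole intervention will take place in 3 different school centres and health care centres". The children's physical activity sessions use the schools' sports equipment. For parents the text has "the theoretical sessions for parents at the same school or at the health care centre next to the school". The behaviour strategy sessions, which bring parents and children together, are placed at both the school and the health care centre.

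On the three weekend activities (component d), the same section says that participants' "friends or relatives will be also invited to take part in the activities". It makes no exception for families enrolled in CG.

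The Counselling group section places CG visits at the paediatrician's office, delivered by the child's "nurse or/and paediatrician".

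**The concern.** Children are randomised individually within each healthcare paediatric unit (HPU), so every unit can have families in both arms. Having both arms within each unit is a sound way to balance centre effects, but it makes separation during delivery matter. The authors recognise this and rely on keeping NP away from the health centre. If part of NP is delivered at a health care centre after all, the separation described in the Discussion is not the one that will operate.

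At stake is the contrast that the trial exists to estimate, NP against counselling. If NP is effective, a CG family that receives some of it moves the CG result toward the NP result. That loss is hard to recover in analysis: an intention-to-treat comparison keeps the dilution, and the protocol describes an attendance register for scheduled sessions, not a record of CG families' exposure to NP. The Sample size section states an allowance for dropout (20%) and none for contamination.

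**Working it through.** The protocol gives no contamination figure, so there is nothing to reproduce. The check sets the passages side by side.

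**Step 1. Do the arms share units?** Yes. The Randomization section stratifies by 7 age groups within each of 16 HPUs. The Recruitment strategy section has each HPU alternate between its intervention list and its CG list. Both arms therefore come from the same units by design, which agrees with the Discussion's own statement of the risk.

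**Step 2. Does the school-venue safeguard hold for each NP component?**

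| NP component | Venue in the Nereu programme section | Agrees with the Discussion's external school? |
|---|---|---|
| Physical activity sessions (90) | School | Yes |
| Parent sessions | School or neighbouring health care centre | Not necessarily |
| Behaviour strategy sessions (3) | Both school and health care centre | No |
| Weekend activities (3) | Outings, such as skiing or a water party | Not a health-centre venue, but open to guests |

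The direct contradiction covers two components, the parent sessions and the behaviour strategy sessions. Table 1 numbers 21 sessions in all. Numbers 6, 15 and 20 are the three behaviour strategy sessions and number 21 is the closing party, which leaves 21 − 3 − 1 = 17 parent sessions. Adding three behaviour strategy sessions to 21 parent sessions would appear to count the same sessions twice.

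**Step 3. Does the second safeguard close the gap?** No. Separate assessment days keep the groups apart at the measurement visits (baseline, end of intervention, and 6 and 12 months later). They do not bear on who is present where during the 8 months of sessions.

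**Step 4. Do the weekend activities contradict the Discussion?** No. The Discussion's measures concern venue and assessment days and are silent on guests. The open invitation is a gap. CG families live in or near the same municipality and attend the same units, so an NP family's friends or relatives could include them, and nothing in the text prevents it.

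**Step 5. Is exposure of CG families stated anywhere?** No. The document does not say whether the health care centres used for NP are among the 16 HPUs, whether they are places where CG counselling is given, or whether NP nurses are also CG children's nurses.

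**The case against.** The strongest reply is that the venue mismatch is a matter of wording and that contamination is nowhere demonstrated. The centres are described as recruited specially for the intervention and are not identified with the recruiting units. NP sessions are closed groups of at most 15 children and parents, while CG visits are individual and last 10 minutes, so sharing a building does not by itself deliver NP content. The largest component, the 90 exercise sessions, stays in schools. The Discussion says only that the authors will try to prevent contamination. Any dilution would also work against NP and could not create a false benefit. Finally, the stated aim is to test a tool for health centres, so an absolute ban on health-centre venues would change what is being evaluated.

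Much of this stands. It rules out any claim that CG families will be exposed, and it is why the fix below leaves room for a health care centre. It does not remove the contradiction: the venue that the Discussion relies on is not the venue that the intervention section gives.

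A reader might go further and infer that nurses will carry NP into CG counselling, since the Nereu course "has been addressed specially to teach and help coaches, nurses and physical activity professionals" and trained nurses deliver parent sessions, while CG counselling comes from the child's own nurse or paediatrician. The document does not support that. It neither says nor excludes that the same nurses serve both arms, and the training of nurses contradicts nothing in the Discussion. Barring trained nurses from CG could also replace the child's own nurse and so alter the comparator.

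**Conclusion.** The point holds in a limited form. The Discussion's school-venue safeguard and the intervention section's venues cannot both describe the trial for the parent and behaviour strategy sessions, and they must be reconciled. Separately, the open invitation to weekend activities is a route that neither safeguard covers.

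If NP is effective and CG families were exposed, the bias would be toward no difference. Its size cannot be derived: there is no contamination rate, and shared centres or nurses are possible but not stated. A reader might want to shrink the planned effect size of 0.60 by some percentage, but nothing in the document supports a particular value. Nor is it right to say that three of the four components breach the safeguard. Two conflict with the stated venue, and the weekend outings raise a different issue.

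The correction is worth making because it is cheap and protects the main contrast.

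**What to change.** 1. Reconcile the Nereu programme section with the Discussion. Hold the parent and behaviour strategy sessions in the three schools already recruited. If a health care centre is used, specify that it is one that does not deliver CG counselling. Reword the Discussion so that it states the venue rule actually applied.
2. Under weekend extra activities, add that families enrolled in CG are not invited to NP activities during the trial. Other friends and relatives can still come, so the social-support purpose is kept. CG children are in any case offered the programme after follow-up.

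The cost is protocol wording, room bookings in schools already in use, and somewhat less choice of venue. No extra participants, visits or measurements are needed, and no change to who delivers CG counselling is proposed.

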## Abbreviations

NP: Nereu programme; CG: Counselling group; HRQOL: Health related quality of life; IDIAP: Primary Care Research Institute – Jordi Gol of Lleida; HPU: Healthcare paediatric unit; CEIC: Clinical Research Ethics Committee; PA: Physical activity; BMI: Body Mass Index; BMI SD sore: Body Mass Index standard deviation; WC: Waist circumference; WHtR: Waist-to-height ratio.
